#### 8.1.2 Intermediate Blood Pressure Measurement

Four weeks after starting intake, blood pressure will be measured (see protocol “Blood Pressure Measurement”).

The results of the measurements will be recorded in the participant’s file.

#### 8.1.3 End Visit

Eight to a maximum of nine weeks after starting intake, the participant will be invited for a final visit.

The visit includes the following actions:

- Measure blood pressure 3 times (see protocol “Blood Pressure Measurement”)
- Complete Food Frequency Questionnaire (FFQ)
- Complete final questionnaire
- Measure weight and waist circumference
- Blood sampling by a nurse (34 mL) (see protocol “Blood Sampling”)
  - o 2x Serum tube (2 × 7 mL)
  - o 3x EDTA tube (3 × 4 mL)
  - o 1x Glucose tube (1 × 4 mL)
  - o 1x Homocysteine tube (1 × 4 mL)
- Unblinding
- Provide book voucher
- Return Tensiofytol® packaging if the participant received placebo during the study

## 8.2 Sample Processing and Analyses

### 8.2.1 Sample Processing

Two EDTA tubes will be centrifuged and divided into aliquots of plasma, red blood cells, and buffy coats according to the protocol “Sample Collection.”

One serum tube will be centrifuged and divided into serum aliquots according to the same protocol.

### 8.2.2. Analyses

#### **Glutathione (GSH)**

GSH levels will be determined in red blood cells using HPLC-ECD according to the protocol “GSH Determination.”

The analysis will be performed by NatuRAPT.

#### **MDA**

MDA will be measured in plasma using ELISA kit E-EL-0060 from Elabscience® according to the provided protocol.

The analysis will be performed by NatuRAPT.

#### **oxLDL**

oxLDL will be measured in plasma using ELISA kit 10-1143-01 from Mercodia according to the provided protocol.

The analysis will be performed by NatuRAPT.

#### **Blood Parameters**

The remaining blood samples will be sent to:

Clinical Laboratory AML  
[name]  
[name]

The following analyses will be requested:

- Hemoglobin
- Creatinine and eGFR
- Total cholesterol, HDL, LDL, Cholesterol/HDL ratio, non-HDL, triglycerides, Apo A1, Apo B, Lp(a), CRP-US, and homocysteine
- Fasting glucose, Hemoglobin A1c, HbA1c (IFCC)
- Fasting insulin and fasting C-peptide

## 8.3 Data Management

Research data will be collected and managed using REDCap electronic data capture tools, hosted by the University of Antwerp.

REDCap (Research Electronic Data Capture) is a secure, web-based software platform designed to support data capture for research studies, providing:

1. An intuitive interface for validated data entry;
2. Audit trails for tracking data manipulation and export procedures;
3. Automated export procedures for data downloads to common statistical packages;
4. Procedures for data integration and interoperability with external sources.

## 8.4 Screening Procedures

During screening, the following specific actions will be performed:

1. Obtain informed consent (see §10.2 Informed Consent)
2. Complete contact form  
The following contact details will be collected from the potential participant:
  - First and last name
  - Address
  - Phone number and email address
3. Check inclusion and exclusion criteria
  - Blood pressure measurement (see protocol “Blood Pressure Measurement”)
  - Complete inclusion checklist by the investigator
  - Complete baseline questionnaire by the participant
4. Collect physical parameters
  - Waist circumference
  - Height
  - Weight

## 8.5 Adverse Events and Serious Adverse Events

### 8.5.1 Definitions of AE and SAE

#### **Adverse Event (AE)**

Any undesirable or unfavorable medical occurrence, including abnormal signs (e.g., abnormal physical examination or laboratory findings), symptom, or illness in a participant, that is temporarily associated with the participant's involvement in the study, whether or not considered related to study participation.

#### **Serious Adverse Event**

Any event that:

- Results in death
- Is life-threatening
- Requires hospitalisation or prolongs hospitalisation
- Causes persistent or significant disability or incapacity
- Results in a congenital anomaly or birth defect
- Is considered by the investigators to pose significant hazards

### 8.5.2 Time Period and Frequency for Collecting AE and SAE Information

Throughout the study, from the start of intake until the final visit, AE and SAE data can be collected. After the study ends, participants will not be actively asked whether AEs or SAEs occurred.

During the final visit, a questionnaire will be completed asking about side effects or discomfort.

At the intermediate blood pressure measurement, there is an in-person contact moment where participants are asked how they tolerate the study product.

### 8.5.3 Identifying and Recording of AEs and SAEs

Participants have the contact details of the investigators and the principal investigator – medical monitor. AEs and SAEs can be reported this way. In case of an SAE, investigators and the medical monitor must be notified immediately.

At in-person visits, participants are asked how they tolerate the study product. Any comments are noted.

During the final visit, participants complete the final questionnaire, which asks about side effects and their severity. If possible, a start and end date for each complaint will be specified.

AEs and SAEs are recorded in the “Adverse Events / Serious Adverse Events” register. For each event, a description, start and end date, outcome, severity, and actions taken are documented.

It is then assessed whether the AE meets the criteria for SAE and whether it may be related to the treatment.

This assessment is done in consultation with the principal investigator – medical monitor.

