| Week 0                                                                                                                                                                                                                                                                                                                                                                                 | Week 4 after start treatment                                                                                | Week 8 – 9 after start treatment                                                                                                                                                                                                                                                                                                                  |
| 
 
Review and signing of Informed Consent Form
 
Complete contact form
 
Blood pressure measurement
 
Check inclusion and exclusion criteria
 
Complete Food Frequency Questionnaire
 
Complete start questionnaire
 
Measure weight, height, and waist circumference
 
Blood sampling
 
 | 
 
Blood pressure measurement
 
Adverse event inquiry
 
 | 
 
Blood pressure measurement
 
Complete Food Frequency Questionnaire
 
Complete end questionnaire
 
Measure weight and waist circumference
 
Unblinding
 
Provide book voucher and Tensiofytol® packaging if the participant received placebo during the study
 
 |

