## 4.2 Rationale for Trial Design

Randomised double-blind placebo-controlled studies are considered the gold standard.

The study is randomised so that unknown or unmeasurable variables do not lead to biased or incorrect results.

The study is double-blind to prevent researchers from treating the groups differently. This approach avoids bias in confirming the hypothesis and interpreting results. It also prevents a disproportionately large placebo effect.

The study is placebo-controlled so that psychosomatic effects do not influence the study outcome.

Studies investigating the effect of olive extract or combination preparations containing olive extract on blood pressure and cholesterol have observed changes in these parameters after an 8-week intervention [10,11]. The intervention in this study lasts 8 weeks but may be extended to 9 weeks for practical reasons.

The primary objective of this study is to assess the influence of the preparation on blood pressure. For this reason, both systolic and diastolic blood pressure will be measured during the screening visit, after 4 weeks, and at the final visit.

To observe changes in oxidative stress markers, MDA, oxLDL, and GSH will be measured in plasma samples collected during the screening and final visits.

At the final visit, participants will be asked about any experienced side effects to evaluate product tolerance.

Total cholesterol, HDL, LDL, non-HDL, remnant cholesterol, triglycerides, apolipoprotein A1, apolipoprotein B, and lipoprotein(a) will describe the participant's lipid profile. These parameters will be determined at the start and end of the study.

Additionally, BMI, waist circumference, fasting glucose, haemoglobin A1c, insulin, and fasting C-peptide will be monitored because abdominal obesity and glucose intolerance are components of MetS.

Haemoglobin, creatinine, ultra-sensitive C-reactive protein, and homocysteine will also be monitored as these parameters are linked to cardiovascular risk.

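### Adverse events are defined regardless of cause, but the questions described to participants are framed around the product, so events they do not link to it may be under-recorded

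*Protocol*

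**What the plan says.** Protocol section 8.5.1 defines an adverse event as any unfavourable medical occurrence during participation, "whether or not considered related to study participation". Section 8.5.3 sets the order of work. Events go into a register, and seriousness and possible relation to treatment are then assessed in consultation with the medical monitor.

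The questions put to participants are described in several places:

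- Section 1.3, week 4: "Adverse event inquiry".
- Section 8.5.2, week 4: "there is an in-person contact moment where participants are asked how they tolerate the study product".
- Section 8.5.2, final visit: "During the final visit, a questionnaire will be completed asking about side effects or discomfort".
- Section 8.5.3, visits in general: "At in-person visits, participants are asked how they tolerate the study product", followed by "Any comments are noted".
- Section 8.5.3, final questionnaire: "which asks about side effects and their severity".
- Section 4.2, final visit: "participants will be asked about any experienced side effects to evaluate product tolerance".

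Section 8.5.3 also gives participants contact details through which they can report events themselves, and requires immediate notification of serious events. Side effects are a secondary endpoint (sections 1.1 and 3.2), and section 3.1 states that tolerance will be evaluated.

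**The concern.** A definition that ignores cause works only if events reach the register before anyone judges their cause. A question about how the product is tolerated, or about side effects, asks the participant to make that judgement first. Someone who had an infection, a fall or a visit to the doctor and sees no link to the capsules can truthfully answer that there is nothing to report. The medical monitor's assessment would then work on a set of events already filtered by participants' own views on causality.

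An effect of the product that participants do not recognise as such is the kind of event most easily lost. A low event count could then partly reflect the question asked, and a reader of the results could take a list of perceived side effects for a full account of adverse events.

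**Working it through.** There is no stated figure to reproduce. The check sets the definition beside each description of how events are collected.

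1. **Definition (8.5.1).** Any unfavourable occurrence counts, whatever its cause.

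2. **Order of steps (8.5.3).** Recording comes first and relatedness second. Nothing in the protocol asks the participant to decide on cause.

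3. **Active questions with described content.** Section 2.2 (Risk Summary) speaks of possible side effects, and section 4.2 of side effects for the purpose of judging tolerance. Section 8.5.2 speaks of tolerance at week 4 and of side effects or discomfort at the end. Section 8.5.3 speaks of tolerance at visits, and of side effects and severity in the questionnaire. Only the word discomfort reaches beyond perceived product effects, and section 8.5.3 omits it. No section describes a question about new illness, injury, medical contact or new medicines.

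4. **The week-4 contact.** Section 1.3 lists a general adverse event inquiry without giving its content. Section 8.5.2 gives the content, and it is tolerance. Section 8.1.2, which describes the same contact, lists only the blood pressure measurement. These three accounts do not agree.

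5. **The final visit.** Sections 1.3 and 8.1.3 list the end questionnaire and no separate adverse event inquiry. In both lists the questionnaire comes before unblinding, and section 4.1 places disclosure after all data are collected.

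6. **Other routes.** Participants may report events on their own initiative, and any comments at visits are noted. Both routes depend on the participant raising the matter.

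7. **Tracing one event.** Take an infection in week 6 that the participant does not connect with the capsules. It meets the definition. It falls after the week-4 contact, and the final questionnaire, as described, asks about side effects or discomfort. It is recorded if the participant volunteers it or counts it as discomfort, and otherwise not. An upset stomach blamed on the capsules would be recorded directly.

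8. **Effect on the comparison.** For events participants do not attribute to the product, let the true rates be pT (product) and pP (placebo), and let a share c of them be recorded. The recorded rates are c × pT and c × pP. If c is the same in both arms, their ratio is (c × pT)/(c × pP) = pT/pP, which is unchanged. Their difference is c × (pT − pP), which shrinks towards zero. The recorded incidence in each arm is too low by the factor c. The documents give no value for c, so the shortfall cannot be sized.

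**The case against.** The case on the other side has several sound parts.

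- **It is not only tolerance and side effects.** The schedule names an adverse event inquiry and section 8.5.2 includes discomfort. This stands, and a claim that participants are asked only about product effects would be wrong. The schedule entry has no content of its own, however, and section 8.5.2 fills it with a tolerance question.
- **Events are not bound to be lost.** Comments are noted, spontaneous reports are accepted and serious events must be notified at once. A reader might infer that events not blamed on the capsules are simply missed. The text supports only that they may be under-recorded, because noting answers to a narrow question does not widen it and spontaneous reporting is passive.
- **The endpoint is named side effects.** A questionnaire on side effects measures that endpoint as named. This stands: the mismatch is with the adverse event definition and register.
- **Blinding protects the comparison.** Product and placebo share appearance and label (sections 4.2.1 and 6.1), and the questionnaire precedes unblinding. A reader might infer that reporting differs by the arm participants believe they are in. That is possible, but nothing in the protocol shows it.
- **The instruments are not shown.** The final questionnaire is a separate document, and the protocol is a machine translation from Dutch. The actual items may be broader than the summaries. This cannot be settled here, although the same framing recurs in sections 2.2, 4.2, 8.5.2 and 8.5.3.

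**Conclusion.** The point holds in a limited form. The active questions described in sections 8.5.2 and 8.5.3 are narrower than the definition in section 8.5.1 and than the week-4 entry in section 1.3. Followed as written, the plan would tend to under-record events that participants do not attribute to the product, probably in both arms, before relatedness is assessed. This weakens statements about overall adverse event incidence more than it biases the comparison of side effects between arms.

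No numerical size can be given. It is tempting to take the 95% upper bound for zero events among 28 participants, 1 − 0.05^(1/28) = 10.1%, and divide it by a capture share of 75% or 50% to get 13.5% or 20.3%. The first figure applies to any group of 28 whatever the question asked. The other two rest wholly on an assumed capture share that has no basis in the documents.

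The conclusion assumes that the week-4 prompt and the final questionnaire match their descriptions in the protocol, and that under-recording is similar in both arms while blinding holds.

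**What to change.** Reconcile sections 1.3, 8.5.1, 8.5.2 and 8.5.3 around one cause-neutral question, and list it in section 8.1.2 as well. At week 4 and in the final questionnaire, ask about any new or worsened symptom, illness, injury, doctor's visit or new medicine since the last contact, whatever the cause. The final questionnaire already precedes unblinding, so the order of the visit need not change. Leave relatedness to the existing medical-monitor step, and report all events and related events by arm.

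Section 4.4 gives February 2024 as the end of recruitment. If data collection is already complete, the remedy lies in the reporting: describe the results as elicited side effects and not as complete adverse event incidence, and give the wording of the questions used.

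The cost is one reworded interview prompt and one questionnaire item, plus a few more unrelated minor events to log.

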#### **8.5.4 Follow-up of AEs and SAEs**

After the study ends, participants will not be actively asked whether AEs or SAEs occurred.

If a complaint began during study participation but has not been resolved, no end date will be recorded.

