## 4. Trial Design

### 4.1 Description of Trial Design

This is a randomised, placebo-controlled, double-blind study. It includes 56 participants, equally divided into 2 groups (28 participants per group). One group will receive Tensiofytol®, and the other will receive a placebo.

Participation in this study will take a maximum of 10 weeks. The potential participant will be invited for a screening visit. If eligible, the participant will be randomised. The study product will then be delivered to the participant as soon as possible. Intake of the study product must start no later than 1 week after the screening visit. The participant must then take the study product or placebo daily. An interim blood pressure measurement will take place 4 weeks after starting intake. The final visit will be scheduled 8 to a maximum of 9 weeks after starting intake. After the final visit, the participant will be unblinded, marking the end of participation.

Participants will be stratified by sex and then randomised into 2 groups. This will occur 1 to 2 days after the screening visit, once all results are available.

This study is double-blind. The investigators do not know which group the participant is assigned to. The participant will be informed of the treatment they received during the final visit, after all data have been collected. The randomisation list and unblinding at the final visit will be handled by a separate study staff member responsible solely for these tasks.

This is a single-centre study. Participants will be enrolled by researchers from the NatuRAPT research group.

Statistical analysis will be performed after all data from all participants have been collected. No interim analysis is planned.

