### 6.3 Dosing and Administration

The participant must take 3 capsules orally at the same time. This should be done with the evening meal for 8 weeks or until the evening before the final visit (maximum 9 weeks after starting intake).

The study product should be taken while sitting upright and with a glass of water.

No dose adjustments are allowed.

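### Section 8.5.4 provides no study-initiated follow-up of adverse events or SAEs still unresolved at the final visit or at early stop, so their final outcome, later seriousness and relatedness may never be known

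*Protocol*

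**What the plan says.** - **Collection window.** Protocol section 8.5.2: "Throughout the study, from the start of intake until the final visit, AE and SAE data can be collected". Section 4.1 sets the end of participation: "After the final visit, the participant will be unblinded, marking the end of participation".
- **Follow-up.** Section 8.5.4 consists of two sentences: "After the study ends, participants will not be actively asked whether AEs or SAEs occurred" and "If a complaint began during study participation but has not been resolved, no end date will be recorded". SAEs get no separate provision.
- **Register.** Section 8.5.3: "For each event, a description, start and end date, outcome, severity, and actions taken are documented". Each event is then assessed for seriousness and for a possible relation to treatment, in consultation with the medical monitor. For the final questionnaire, the same section qualifies the dates: "If possible, a start and end date for each complaint will be specified".
- **Seriousness.** Section 8.5.1 includes criteria that depend on how an event develops, such as death, prolonged hospitalisation, congenital anomaly, and "Causes persistent or significant disability or incapacity".
- **SAE reporting.** Section 8.5.5 requires a form, notice to the medical monitor and a report to the Ethics Committee.
- **Early stop.** Section 7.1.1 allows stopping because of discomfort from the treatment. Section 7.1.2 makes stopping a reason for exclusion from the study.
- **Pregnancy.** Section 8.6.1 excludes a participant who becomes pregnant and provides no follow-up.

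**The concern.** Tolerance is a stated objective (section 3.1) and side effects are a secondary endpoint (section 3.2). For an event that starts late in the intake period, the useful safety information often comes after the final visit: whether the event resolved, whether it became serious, and whether it went away once intake stopped. Section 8.5.4 is where a plan to obtain that information belongs. Instead it says that routine questioning stops and that the end date stays blank.

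Participants who stop early because of discomfort are plausibly among those with product-related events. Apart from the return of capsules, the protocol describes no later step for them.

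A team that follows the text as written could therefore report an SAE once and never learn its outcome. It could also leave as non-serious an AE that later meets a criterion in section 8.5.1. Safety follow-up is a protocol procedure and this protocol has a section for it, so the point cannot be left to a statistical analysis plan.

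**Working it through.** The protocol gives no figure to reproduce, so the check sets the sections side by side.

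1. **Is there follow-up of an open event after the final visit?** Collection runs to the final visit (8.5.2) and participation ends there (4.1). Section 8.5.4 adds no contact, and 8.5.5 adds reporting but no follow-up report. None is stated, for SAEs included.

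2. **Is there follow-up after early stop?** Sections 7.1.1 and 7.1.2 cover return of capsules and exclusion from the study. They do not mention the event that caused the stop. None is stated.

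3. **End date.** Section 8.5.3 lists an end date for each register entry without exception, and 8.5.4 leaves it blank for unresolved events. The qualifier in 8.5.3 concerns the questionnaire, not the register. Section 8.5.4 can be read as a specific exception to the general list, so this is a loose end in the wording.

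4. **Outcome.** Not resolved at the final visit is a recordable outcome, so the field can be filled. The final outcome is what may be missing.

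5. **Seriousness.** Section 8.5.3 requires each AE to be tested against 8.5.1. Some criteria can be judged at onset: life-threatening, requiring hospitalisation, posing significant hazards. Others may become apparent only later: death, prolonged hospitalisation, persistent disability, congenital anomaly. No step re-applies the later ones to an event that was open at the final visit.

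6. **Relatedness.** Section 6.3 sets intake as follows: "This should be done with the evening meal for 8 weeks or until the evening before the final visit (maximum 9 weeks after starting intake". That visit falls 8 to 9 weeks after the start (8.1.3). Time off product before that visit therefore ranges from under a day to about a week (9 − 8 = 1 week). For many late events, little or nothing will be seen of their course after stopping.

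7. **Pregnancy.** Section 8.5.1 counts a congenital anomaly or birth defect as serious, while 8.6.1 provides no follow-up that could detect one.

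**Illustration only.** The protocol gives no event durations. Assume that onset is constant over an intake period of T days and that durations are exponential with mean m. The share of events still open at the final visit is then (m/T)(1 − exp(−T/m)).

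| Assumed mean duration m | T = 56 days | T = 63 days |
|---|---|---|
| 7 days | 0.125 × (1 − e^−8) = 12.5% | about 11% |
| 14 days | 0.25 × (1 − e^−4) = 24.5% | about 22% |
| 28 days | 0.5 × (1 − e^−2) = 43.2% | about 40% |

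These are shares of an unknown, possibly very small, number of events.

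**The case against.** The strongest reply is that little is lost. Events from the start of intake to the final visit are captured in both arms, so the comparison of incidence is intact. Ending routine questioning does not forbid the team from following an SAE already notified to the medical monitor and the Ethics Committee. The SAE form and the register are separate documents, not at hand, and may ask for follow-up. All of this stands, and it limits the point to outcome, later seriousness and relatedness. It does not supply a follow-up rule in the protocol.

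A reader might infer four stronger things that the text does not support:

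- **That open events are closed at the final visit.** A blank end date leaves them recorded as ongoing.
- **That 8.5.4 contradicts 8.5.3 or 8.5.1.** An unresolved status is an outcome, the blank end date can be an exception, and 8.5.4 does not alter the seriousness criteria. The disability criterion also has a limb for significant disability that need not wait for persistence.
- **That participants lose any safety contact.** Section 8.5.3 says that they hold the contact details of the investigators and the medical monitor. What is missing is contact initiated by the study.
- **That every late event has less than one day off product.** Section 6.3 also allows intake to end at 8 weeks, which leaves up to about a week before a visit at week 9.

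A further objection concerns the remedy. Participants are unblinded at the final visit (4.1, 8.1.3), and those on placebo are then given 112 capsules of the product (4.3, 5.8). Later calls would be unblinded and, for some, made while the participant takes the active product. This is correct and must be dealt with in the fix.

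**Conclusion.** The point holds as a gap in safety follow-up. As written, the protocol provides no study-initiated follow-up of an AE or SAE unresolved at the final visit or at early stop, and no SAE follow-up report. Final outcome, any later change to serious, and information for the relatedness judgement may never be obtained.

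The effect is limited to how complete the information is for one secondary endpoint and to individual safety. The primary analysis, the α-level, the sample size and AE incidence up to the final visit are untouched. The number of events affected cannot be derived from the protocol. The 12% to 43% range shows only that open events need not be rare if durations are of the assumed order. The conclusion does not depend on it. The amendment is worth making because it is cheap in a trial of 56 participants.

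**What to change.** 1. **Amend 8.5.4.** Every SAE, and every AE judged possibly related and unresolved at the final visit or at early stop, is followed by phone until it is resolved, stable or has reached a date set by the medical monitor. The outcome is entered in the register and seriousness is re-assessed at closure. Routine questioning about new events may still end at the final visit.
2. **Protect the relatedness judgement.** Record it before the participant is unblinded, and mark later information as collected unblinded. For placebo participants, also note whether the supplied product was being taken at the time of the call.
3. **Amend 8.5.3.** State that the register's end date may stay blank while an event is ongoing.
4. **Reconcile 8.5.1 with 8.6.1.** One counts a congenital anomaly as an SAE and the other provides no follow-up after pregnancy.

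**Cost.** About a paragraph of amendment text and a few phone calls, with no extra visit, sample or staff. The affected records close later. The information gained after the visit is unblinded and, for placebo participants, may reflect use of the supplied product. It therefore serves outcome and seriousness better than a blinded comparison between arms.
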